professional caregivers (n=5). All n=220 patients will undergo a detailed neurological and neuropsychological examination before the start of the training (=intervention group) or during the waiting period (=control group) and after the 1.5-year training/waiting interval. Furthermore, an MRI will be performed at both time points. Data analysis will be conducted quantitatively (descriptive statistics, inferential statistics) and qualitatively (content analysis).

This study promotes the development of computer-based tablet-PC training programs for the target group of Alzheimer's dementia in clinical practice.

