#### **4.2.2.3. Randomization and Blinding**

##### Randomization of Participants with Dementia

A randomization plan will be prepared in advance. Allocation to the Intervention Group (IG) and Control Group (CG) will be determined beforehand using a random list created in Matlab. Among participants 1-110, 70% will be allocated to the IG and 30% to the CG. For participants 111-220, 30% will be allocated to the IG and 70% to the CG. This ensures that, in the case of potential enrollment difficulties, a sufficient number of participants receive the intervention. It should be explicitly noted that the aim is to provide the intervention rather than achieving equal distribution between the IG and CG. At the Department of Neurology, only the Study Nurse will know whether a patient is in the IG or CG. The investigators (neurologist, neuropsychologist) will not know the group allocation.

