## **GENETIC ANALYSES**

For the study, ApoE genotyping is required. The ApoE4 genotype is associated with faster progression of Alzheimer's disease, so it is crucial to ensure that there is no imbalance in the frequency of ApoE4 carriers between the training group and the comparison group.

Given that DNA extraction is necessary, we will take this opportunity to ask patients for consent to use their DNA for potential future scientific projects. It is understood that each of these future projects will require a separate ethical review.

All samples will be anonymized, labeled with a code rather than names, and processed. The samples can only be linked to the name of the donor at the University Clinic for Neurology. Should the results of genetic analyses or phenotype data be used in scientific collaborations, it will be ensured that the donor cannot be identified by the collaborating centers. If international collaborations are pursued, these will be specifically submitted to the ethics committee as described above.

At the Neurology Clinic, the following risk genes for Alzheimer's disease are currently being investigated as part of a Next-Generation Sequencing panel: ASNA1, ATP13A2, ATP1A3, ATP6AP2, C19orf12, CHCHD2, COMT, DCTN1, DNAJC13, DNAJC6, EIF4G1, FBXO7, FMR1, FTL, GBA, GCH1, GRN, HTRA2, LRRK2, MAPT, PANK2, PARK2, PARK7, PDE8B, PDE10A, PINK1, PLA2G6, PODXL, POLG, PRKAR1B, PRKRA, PTEN, RAB29, RAB39B, SLC30A10, SLC6A3, SNCA, SPG11, SPR, SYNJ1, TAF1, TENM4, TH, VPS13C, VPS35, ZFYVE26.

Such investigations are possible but depend on appropriate funding.

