## **4.5. Statistics**

### Quantitative Part

The data will be analyzed using IBM SPSS version 24. The significance level is set at  $\alpha = 0.05$ . Descriptive statistics will be presented as mean and standard deviation or as median and quartiles, depending on the type of distribution. Absolute and relative frequencies will be used to describe categorical data. To address the primary research question—whether tablet-based training has a positive effect on cognition—both the primary outcome (performance in the neuropsychological test battery, NTB, global score) and secondary outcome parameters (sub-tests of the NTB and other neuropsychological assessments) will be compared between the intervention group (IG) and control group (CG) using ANCOVA (adjusted for multiple comparisons). Additionally, total brain volume, the volume of brain lobes, hippocampal volume, cerebral microstructure, and functional connectivity will be measured and compared between groups. Other secondary outcome parameters will also be compared between groups using ANCOVA. Pre-post comparisons (ANOVA repeated measures) will provide insights into changes over time. Analyses will be adjusted for age, gender, comorbidities, and education level.

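### The covariate list in section 4.5 names neither the outcome's baseline value nor ApoE4 carrier status, though both are collected and ApoE4 balance is called crucial

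*Protocol*

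**What the plan says.** Section 4.5 (Statistics, Quantitative Part) names the "primary outcome (performance in the neuropsychological test battery, NTB, global score") and says that it and the secondary cognitive outcomes are "compared between the intervention group (IG) and control group (CG) using ANCOVA (adjusted for multiple comparisons"). The other secondary outcomes are handled the same way. A further sentence reads "Pre-post comparisons (ANOVA repeated measures) will provide insights into changes over time". The paragraph then closes with the only list of adjustment variables: "Analyses will be adjusted for age, gender, comorbidities, and education level".

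Baseline values exist. The Summary says that all 220 patients "will undergo a detailed neurological and neuropsychological examination before the start of the training" or, in the control group, during the waiting period. Table 1 schedules the neuropsychological test battery at T0-a and T3, and brain MRI at T0-b and T3.

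On ApoE4, the section on genetic analyses states "For the study, ApoE genotyping is required". It links the E4 genotype to faster progression and adds that "it is crucial to ensure that there is no imbalance in the frequency of ApoE4 carriers" between the two groups. Section 4.2.2.3 says that allocation is "determined beforehand using a random list created in Matlab", with 70% of participants 1-110 and 30% of participants 111-220 going to the intervention group. It mentions no stratification or minimisation.

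**The concern.** In a trial of cognitive decline, the T0 score is normally the strongest available predictor of the T3 score. A model with only the four listed covariates gives up that information. It also leaves any difference in starting cognition between the arms in the estimate.

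The ApoE4 gap is a mismatch inside the protocol. It gives a reason for genotyping, namely balance on a factor it regards as prognostic, but neither the allocation procedure nor the analysis does anything to secure that balance or to correct for its absence.

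The allocation scheme adds to the baseline problem. Because the ratio reverses halfway, the intervention arm is mostly early recruits and the control arm mostly late ones. If the two waves of this convenience sample differ in cognition, the arms will differ too, and the T0 score is the variable that would show it.

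**Working it through.** **Plan's own figures.** The protocol gives no effect size, SD, power or dropout rate, so there is no sample-size result to reproduce. The allocation arithmetic agrees with the stated arm sizes: intervention 0.7 × 110 + 0.3 × 110 = 77 + 33 = 110; control 33 + 77 = 110.

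**Inputs.** From the protocol: 110 per arm, alpha 0.05, the 70/30 then 30/70 split. Assumed: a two-sided test, a T0-T3 correlation r of 0.6 to 0.8, 40% to 60% ApoE4 carriers, equal SD at T0 and T3, no dropout, and no contribution from the four listed covariates.

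**Precision.** With the T3 SD set to 1, the variance of the analysed quantity is 1 for T3 scores alone, 2(1 − r) for a change score, and 1 − r² for ANCOVA with baseline. The detectable difference at 80% power is (1.960 + 0.842) × √(2/110) = 0.378 SD for T3 alone, multiplied by the square root of the variance for the others.

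| r | Variance, change | Variance, ANCOVA | Cut vs T3 alone | Cut vs change | Detectable, change | Detectable, ANCOVA |
|---|---|---|---|---|---|---|
| 0.6 | 0.80 | 0.64 | 36% | 20% | 0.338 | 0.302 |
| 0.7 | 0.60 | 0.51 | 49% | 15% | 0.293 | 0.270 |
| 0.8 | 0.40 | 0.36 | 64% | 10% | 0.239 | 0.227 |

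The equivalent sample-size factor is 1/(1 − r²) = 1.56 to 2.78 against T3 alone. Against a change score it is 2(1 − r)/(1 − r²) = 2/(1 + r) = 1.25 to 1.11. For a true difference of 0.378 SD, power is 80% on T3 alone, about 88%, 95% and 99% on change (r = 0.6, 0.7, 0.8), and 93.8%, 97.5% and 99.7% with baseline-adjusted ANCOVA.

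**Early and late recruits.** The share of first-wave patients is 77/110 = 70% in the intervention arm and 33/110 = 30% in the control arm, a gap of 0.40. If the waves differ in baseline cognition by 0.25 to 0.5 SD (assumed), the arms differ in expectation by 0.40 × 0.25 = 0.10 to 0.40 × 0.5 = 0.20 SD before training. If that gap persists unchanged to T3, baseline ANCOVA removes a fraction r of it, that is 60% to 80%. If the gap acts on T3 only through the T0 score, all of it is removed.

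**ApoE4.** The standard error of the difference in carrier proportion is √[p(1 − p)(1/a + 1/b)].
- At 110/110 it is 0.066 to 0.067. The chance of a gap above 10 percentage points is 13% to 14% by the normal approximation; the exact chance of 10 points or more is 15% to 16%.
- If enrolment stopped after 110 patients (77/33), it is 0.102 to 0.104 and the chance is about 33% to 34%.
- Effect on the estimate: if carriers score 0.3 SD lower (assumed), a 10-point gap shifts the treatment difference by 0.10 × 0.3 = 0.03 SD. The standard error of that difference is √(2/110) = 0.135 SD at 110/110 and √(1/77 + 1/33) = 0.208 SD at 77/33.

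**The case against.** The strongest reply is that the baseline omission may be only one of wording. ANCOVA on a test measured before and after treatment is often understood to include the baseline value. The list is not called exhaustive, and it closes a paragraph that also covers the repeated-measures ANOVA, so it could be read as extra adjusters common to every analysis. A statistical analysis plan could complete the model. This reply stands in part. A reader might infer that the primary analysis compares raw T3 scores and ignores baseline, but section 4.5 never says that the dependent variable is the T3 level; it could be change. T0 data also enter through the pre-post analysis. The full 1.6- to 2.8-fold sample factor is therefore an upper bound. The listed covariates will already explain some of what baseline explains, which lowers it further.

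What does not stand is that the word ANCOVA settles the matter. Four listed covariates already make the model an ANCOVA, so someone following the text literally would leave baseline out. Nor is this merely detail left for later: the protocol fixes a list, and that list does not fit its own statement on ApoE4.

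On ApoE4, a reader might infer that the treatment estimate is biased. The documents do not support that. Imbalance under randomisation is chance imbalance, already covered by the significance level, and the likely shift is small beside the standard error. The genotyping could also be meant only to check balance, although the protocol speaks of ensuring it.

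**Conclusion.** The point holds as a correctable weakness and should be fixed. The list in 4.5 names neither variable, both are collected, and nothing in allocation or analysis secures the ApoE4 balance that the protocol calls crucial.

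The main cost of following the list literally is precision: a variance up to 36% to 64% lower is forgone if T3 scores are compared, but only 20% to 10% if change is compared, under the assumed correlations and before allowing for the other covariates and dropout. The second cost is uncorrected imbalance. For ApoE4 this is minor in expected size. For starting cognition it could reach 0.10 to 0.20 SD if early and late recruits differ as assumed, which the documents neither show nor exclude.

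It would go too far to call the primary test invalid or the omission fatal. Neither omission by itself breaks the type I error of a randomised comparison, the recruit-wave difference is hypothetical, and section 4.1 describes the study as exploratory.

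**What to change.** In section 4.5, state that each T3 outcome also measured at T0 is compared between groups by ANCOVA with its own T0 value and ApoE4 carrier status (yes, no, missing) as covariates, in addition to age, gender, comorbidities and education. The missing category is needed because section 4.6.1 makes genetic analysis depend on written consent.

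The cost is one sentence and up to three degrees of freedom (one for baseline, two for the three-level ApoE4 factor), which is negligible with 220 patients. No new data are required. The sentence should be fixed before group results are seen, so that the choice of primary model is not open afterwards.

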### Qualitative Part

The qualitative interviews will be organized and coded using the software program MAXQDA and analyzed through qualitative content analysis (Kimberly & Neuendorf, 2017) by the Institute of Nursing Science.

## **4.6. Ethical Considerations**

### **4.6.1. Informed Consent**

Only individuals who provide prior written informed consent will be included in the study. For participants with dementia who have a representative or legal guardian, written informed consent will be obtained from these representatives. All participants can withdraw from the study at any time without providing reasons. All examinations, except for blood draws, are non-invasive. Additionally, all procedures, including the 3T MRI, are conducted in clinical routine. Genetic analyses are performed in accordance with legal

requirements. The genetic analyses are conducted solely for scientific purposes and only with the written consent of the donor. All samples are processed anonymously and coded without names. Samples can only be linked to the University Clinic for Neurology with the name of the donor.

If results from genetic analyses are shared, measures will be taken to ensure that the donor cannot be identified by the collaborating centers. Except for blood draws, no harm or burden is anticipated for participants. The benefit-risk ratio is therefore considered to be high.

#### **4.6.2. Data Protection**

##### **4.6.2.1. Data Protection for Questionnaires and Interviews**

Each study participant is assigned an individual anonymized code upon inclusion or randomization, which is recorded at the University Clinic for Neurology (UK) and transmitted to the Sozialverein Deutschlandsberg (SVDL) and the Research Coordination (RK). Communication between project partners and any data transfer will occur using this code to ensure participant anonymity. Questionnaires and interviews (both individual and focus groups) are transmitted through a secure, password-protected server from the SVDL to the Medical University of Graz (MUG). All personal data of participants are handled confidentially, and interviews are anonymized during transcription. Access to data for input and analysis is limited to the University Clinic for Neurology - Clinical Department of Neurogeriatrics, the Institute for Nursing Science at MUG, and Joanneum Research Digital (research partners).

##### **4.6.2.2. Data Protection and Privacy for “DaheimAktiv”**

###### „DaheimAktiv“

###### *Login/Backend „DaheimAktiv“*

To use "DaheimAktiv," users must register with an email address and a password, which are encrypted and stored in the database. Only one device (tablet) can be actively used per account, and this device is linked to the user account. The unique serial number of

the device is also recorded and associated with the user. Additional personal data is optional and not required for registration.

#### Completed Units „DaheimAktiv“

"DaheimAktiv" stores a data stream for each completed unit, reflecting the participant's performance during these sessions. This includes data on speed and accuracy in included exercise programs (e.g., error detection, correct/incorrect answers, quizzes). This data is essential for detecting improvements or deteriorations in participants' performance, identifying strengths, and pinpointing areas for further improvement. For general analyses of this target group, the data is anonymized.

#### **4.6.2.3. Data Protection for Fitness Tracker**

The use of the fitness tracker is linked to a user account that must be created by the user through the fitness tracker's application. There is no transmission of log data to the project's central database. Data can only be accessed by the user themselves, using their account credentials.

### **4.7. Benefits/Risks**

#### **4.7.1. Benefits**

The use of the multimodal "DaheimAktiv" serious game on the tablet PC as a non-pharmacological intervention promotes psychological, cognitive, physical, and social abilities. The long-term benefit could be a stabilization of the disease progression. Participants' results support the further development of cognitive training programs on tablet PCs for application in caregiving practice. In particular, participants with dementia provide valuable insights into the individual needs of their target group. According to the systematic review by Span et al. (2013), individuals with dementia should be integrated at all stages of a development project to create valuable, user-friendly, supportive technologies that enhance the quality of life for this group and enable a longer stay in their own home.

#### **4.7.2. Risks**

Psychological (e.g., overload) or physical (e.g., fatigue) stress related to the use of the "DaheimAktiv" tablet PC program may occur. To minimize these stresses, the training programs are tailored to individuals with dementia (e.g., difficulty level, duration), and participants are accompanied and supported by dementia trainers throughout the study. Participants can also contact the research team at any time to discuss any issues.

During MRI imaging, participants may experience discomfort. Each participant can choose to stop the examination at any time. For blood sampling, there is a slight risk of bruising, bleeding, or pain at the puncture site, and in rare cases, the risk of fainting. Participants with a tendency to bleed or a known propensity for collapse are advised against participation. For lumbar puncture, risks include bleeding and bruising, infections and inflammations, circulatory and consciousness disturbances, as well as temporary nerve damage with numbness or paralysis. It is explicitly stated that the lumbar puncture is optional.

Participation in the study can be terminated at any time without giving reasons and without any disadvantages for the patient or their relatives.

## Appendix 1 Data Collection Instruments

*According to the journal's guidelines, copyrighted images have been removed from the published version.*

Translation
